## 7.6 MONITORING

### Monitoring:

Each participating site will be monitored in 6 monthly intervals. Data monitoring will be undertaken throughout the trial, based on a data monitoring and auditing plan (DMAP) devised by the study team. The DMAP has been developed in accordance with ICH GCP guidelines and reflects current best practice for data monitoring practices in investigator-initiated trials. The DMAP includes the following components:

- Data verification on all screening data items (i.e. inclusion and exclusion criteria) on a random sample of 5% of ineligible patients from each site;
- Data verification on all screening data items (i.e. inclusion and exclusion criteria) for every enrolled patient;
- Data verification on the stratification used for randomisation and consent data items and data items related to calculation of the primary outcome and secondary outcomes for every enrolled patient; and
- Data verification on key data items relating to cohort descriptors on a random sample of 10% of enrolled patients from each site.

The original study REDCap database was enhanced to facilitate the DMAP. Each site is monitored by a research co-ordinator from a different trial site. This will be undertaken through a combination of on-site monitoring and remote monitoring using the institutional programme to share desktop computer screens. The remote monitoring will not be recorded or stored and the monitored site is in control of the shared patient screen at all times. During the coronavirus-2019 pandemic (COVID-19), sites are only allowed to use remote monitoring. Each relevant data item is verified individually by comparing the entered value with the value in the source documentation. Where discrepancies are found, the site research co-ordinator and monitor discuss and resolve the discrepancies. Once data monitoring is finalised, the patient's REDCap data entry record is locked in preparation for analysis.

**Study protocol adherence.** Site visits for start up and education to guarantee adherence to the study protocol will be performed at the start and then twice during the study.

## 8 ADVERSE EVENTS AND RISKS

### 8.1 Definitions

Adverse Event (AE) is any untoward medical occurrence in a patient enrolled into this study regardless of its causal relationship to study treatment intraoperatively and ***within the first 48 hours postoperatively.***

Serious Adverse Event (SAE) is any AE that results in:

- Death
- Is life-threatening
- Requires prolongation of existing hospitalisation
- Results in persistent or significant disability/incapacity
- Requires intervention to prevent permanent impairment or damage

**Specific AEs related to NO delivery during CBP: air embolism, severe hypotension during bypass and increased MethHb (MethHb is >3%).** For the purposes of this study the site investigator is responsible for recording all AEs, regardless of their relationship to study intervention, for the period from randomisation until completion of each individual child's participation in the study.

This study is performed in infants and children undergoing high risk cardiac surgical procedures with death or high risk organ support such as ECLS or renal replacement therapy within the expected outcome. We will report all SAE including deaths and the investigators will give clinical recommendations if the death was unexpected and reason for further investigation by the DSMB.

Additional screening for adverse events will occur at the time of patient discharge from hospital.

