### **Measured Parameters.**

**Baseline variables:** Sex, age, weight, primary cardiac diagnosis, secondary diagnoses including comorbidities (prematurity, syndrome), pre-operative disease severity (pre-operative PICU admission and length of PICU admission, ventilation and length of preoperative invasive ventilation, inotrope use and dose, prostaglandin use pre-op, diuretics, afterload reduction, infection pre-bypass). Functional assessment at baseline pre-surgery using parental interview/questionnaire to define POPC. Pre-operative medications: steroids, antibiotics, inotropes, prostaglandin, afterload reducing agents.

**Surgical intervention and bypass:** Data on performed cardiac surgical procedure, RACHS and Aristotle score (scores describing the complexity of the surgical procedure), amount and type of fluids and blood products given during surgery, length of CPB (for every run if several runs during one surgery are required), aortic cross clamp time, deep hypothermic arrest (temperature, duration), and length of NO or control delivery. Steroids given during theatre. Modified ultrafiltration. MetHb, NO.

**Postoperative status:** Data on postoperative cardiovascular status, respiratory status, urine output will be collected. Arterial and central venous (taken from jugular, subclavian, or femoral central venous catheter) blood gas analysis including lactate measurements. Laboratory tests to define organ dysfunction platelets, white cell count, haemoglobin, creatinine, base excess, pH, pCO2, pO2, SataO2, and coagulation. Amount and type of blood products given during first 24 and 48 hours. Amount of fluid given during first 24 and 48 hours. Delayed chest closure and time to chest closure. Arrhythmia (JET, etc). Intravenous steroids given during 48 hours postoperatively. Use of iNO. MetHb. Delirium. Total inotrope hours, post-operative infections, re-intubations, cardiopulmonary resuscitation, necrotising enterocolitis, readmissions to PICU and child status will be collected at 28 days. In the event that the child has been transferred to another healthcare facility, parents are asked to consider permission to access medical records within the consenting process.

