### 8.3 Eliciting adverse event information

Adverse events will be recorded from the time the patient is randomised to the study until end of study participation. Additional screen for AEs will occur at the time of patient discharge from hospital. AEs will be documented from physical examination findings, clinically significant lab results or other documents that are relevant to patient safety.

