### 8.4 Serious adverse event reporting

Any SAE occurring in a study participant will be reported to the HREC within 24-72 hours of detection, in accordance with the safety reporting policy of the HREC. The HREC safety reporting form will be completed, signed and submitted by an investigator.

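### The serious adverse event list in protocol 8.1 covers a prolonged stay but not a new admission, so an adverse event that brings a discharged child back to hospital can be classed as non-serious

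*Combined protocol and SAP*

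**What the plan says.** Protocol 8.1 defines an SAE as an AE with one of five results. Apart from death, they are:

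- "Is life-threatening"
- "Requires prolongation of existing hospitalisation"
- "Results in persistent or significant disability/incapacity"
- "Requires intervention to prevent permanent impairment or damage"

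The protocol gives two time limits for AEs. The AE definition in 8.1 covers events during surgery and "within the first 48 hours postoperatively". Later in 8.1, site investigators must record all AEs from randomisation until the child's participation is complete, and 8.3 repeats this: "Adverse events will be recorded from the time the patient is randomised to the study until end of study participation". Section 7.5 places follow-up at 12 months.

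On reporting, 8.4 says "Any SAE occurring in a study participant will be reported to the HREC", with a limit of 24 to 72 hours from detection. Section 8.2 has the case report form state for each AE whether it is serious. Among the 28-day items, section 7.2 (Measured Parameters) says "readmissions to PICU and child status will be collected at 28 days".

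**The concern.** The hospital criterion presupposes that the child is still an inpatient. Once the child has gone home there is no existing stay to prolong, so an AE that causes readmission has to qualify as serious by another route. If it is not fatal, life-threatening or disabling, and needs no intervention to prevent lasting damage, it is recorded as non-serious.

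Two things follow. First, the report with a fixed deadline in 8.4 is not triggered. Second, seriousness comes to depend on whether the child had been discharged when the event arose, not only on the event itself. Length of PICU and hospital stay are secondary outcomes (3.2), so discharge timing is something the trial hopes to change. Serious adverse events are also a ground on which 10.1 allows the monitoring board to recommend stopping, so the label matters.

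**Working it through.** No arithmetic applies and the plan states no figure to reproduce. The check sets the definition, the windows and the reporting rule side by side.

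**Step 1: is the criterion supplied elsewhere?** It is not.
- Protocol 13.3 grades severity and causality, not seriousness.
- The SAP's safety section and its list of supplementary material contain no SAE definition.
- Protocol 7.2 collects PICU readmissions at day 28 as postoperative status data.
- SAP Appendix S2 adds a PICU readmission within 72 hours of discharge to the ward to the PICU length of stay.
- Neither of the last two makes a readmission an SAE.

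**Step 2: apply the wording to matched cases.** In each row the event meets none of the other four criteria.

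| Event | AE limited to surgery and 48 hours (8.1 definition) | AE to end of participation (8.1 recording rule, 8.3) |
|---|---|---|
| A. Starts within 48 hours; child still in hospital; stay lengthened | SAE | SAE |
| B. Starts within 48 hours; child discharged, then readmitted because of it | AE, not SAE | AE, not SAE |
| C. Starts after 48 hours; child still in hospital; stay lengthened | Not an AE | SAE |
| D. Starts after discharge and more than 48 hours postoperatively; child readmitted | Not an AE | AE, not SAE |

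**Step 3: read the table.** Under the longer window the gap is rows B and D; C and D can be the same complication on the same postoperative day, separated only by discharge status. Under the 48-hour window the gap is row B alone. That row needs an event that starts within 48 hours, does not hold the child in hospital, and later causes a return. Under both windows there is an AE leading to readmission that need not be called serious.

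**Step 4: what depends on the label?** Only SAEs carry the 24 to 72 hour deadline in 8.4. The SAP's between-arm safety comparison is a logistic regression on whether a patient had any AE, serious or not. Events in row B, and in row D where they count as AEs, remain in that comparison and in the planned AE listing.

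**The case against.** The best argument on the other side is that the window conflict is the underlying problem. An SAE must first be an AE. If the 48-hour sentence says what an AE is, and the later sentences only say how long AEs are recorded, most post-discharge events never reach the SAE list. The gas is given only during bypass (6.1), which makes an early, in-hospital safety focus defensible. This stands in part: it makes the gap small under one reading but does not close it, and the text does not settle which reading governs.

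Four stronger readings are tempting, and the documents do not support them.

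- *That such readmissions would go unreported.* Section 10 has the site principal investigator review safety data regularly and promptly tell the ethics committee and the coordinating team of other significant events. The SAP says AE information went to the monitoring board at both interim analyses. What is lost is the defined trigger and fixed deadline; the section 10 route rests on judgement and sets no number of hours.
- *That SAE counts would be biased between arms.* Seriousness does depend on discharge date, but the SAP plans no SAE count by arm.
- *That the number affected can be estimated.* Assuming that 5% to 10% of 1,320 children are readmitted by day 28 gives 1,320 × 0.05 = 66 to 1,320 × 0.10 = 132. The rate is not in the documents. The product also includes planned readmissions, readmissions not caused by an AE, and those already serious on another criterion. It is at most an upper bound under an assumed rate.
- *That the data are already in hand.* Section 7.2 names readmission to PICU. That can include a return from the ward within the same hospital stay, where the prolongation criterion can already apply. Readmission from home to a ward is not a named item.

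**Conclusion.** The point holds as a gap in the safety definition. As written, an AE that causes readmission after discharge and meets no other criterion is non-serious and falls outside the deadline in 8.4, while the same event in an inpatient is serious if it lengthens the stay.

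Its size cannot be stated from the documents. It depends on an unreported readmission rate and on which AE window applies: rows B and D of the table under the end-of-participation window, row B alone under the 48-hour window. The effect is confined to seriousness classification and time-limited reporting. The efficacy analyses and the SAP's any-AE comparison do not use the SAE label. It is worth correcting because the rule, followed faithfully, misclassifies these events and the wording change is small.

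**What to change.** 1. Reconcile the two AE windows in 8.1 and 8.3 and state one period with an explicit end. Any limit kept for a particular purpose should be labelled as such.
2. Reword the hospital bullet in 8.1 so that it covers hospitalisation, including unplanned readmission, as well as prolongation of a current stay. Exclude planned staged surgery.
3. Apply the bullet over the reconciled window to readmissions that the site becomes aware of.

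The cost is a short amendment to 8.1 and 8.3 and more SAE forms. Hospital readmissions other than to PICU are not a named item at day 28, so they would depend on site awareness unless a field is added. The only additional AE screen described is at hospital discharge, and the all-site 12-month contact in 7.5 is a parent survey on quality of life, development and socioeconomic status. Systematic capture to 12 months would therefore need surveillance that the plan does not describe; limiting the rule to readmissions known to the site avoids that. Settling the window will also settle which events enter the SAP's any-AE comparison, so the SAP should cite the same period. No treatment, endpoint or sample size changes.

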### 8.2 Assessment and documentation of adverse events

The description of each AE on the Case Report Form (CRF) will include all of the following:

- A description of the AE;
- The onset date, duration, date of resolution;
- Severity (mild, moderate or severe);
- Seriousness (i.e. is it an SAE?);
- Any action taken;
- The outcome (recovery, death, continuing, worsening);
- The likelihood of the relationship of the AE to the study treatment (Unrelated, Possible, Probable, Definite).

Changes in the severity of an AE will be recorded on the CRF.

AEs characterised as intermittent will be documented for each episode.

All AEs will be followed to adequate resolution or stabilisation, where possible.

**Data Safety Monitoring Board (DSMB).** Consists of one statistician, one independent intensive care specialist (from a non-cardiac centre) and one cardiac surgeon. The DSMB will oversee the study performance, recruitment rate and analysis.

### 8.3 Eliciting adverse event information

Adverse events will be recorded from the time the patient is randomised to the study until end of study participation. Additional screen for AEs will occur at the time of patient discharge from hospital. AEs will be documented from physical examination findings, clinically significant lab results or other documents that are relevant to patient safety.

### 8.4 Serious adverse event reporting

Any SAE occurring in a study participant will be reported to the HREC within 24-72 hours of detection, in accordance with the safety reporting policy of the HREC. The HREC safety reporting form will be completed, signed and submitted by an investigator.

## 9 DATA MANAGEMENT

### 9.1 Data Collection

The investigators are responsible for ensuring the accuracy, completeness, legibility, and timeliness of the data reported. All source documents should be completed in a neat, legible manner to ensure accurate interpretation of data. The investigators will maintain adequate case histories of study participants, including accurate case report forms (CRFs), and source documentation.

#### 9.1.1 Source Data

Source data will be entered directly onto pre-printed CRFs where practical, where this cannot occur in real time, data will be retrospectively entered onto CRFs from hospital records, observation charts and resuscitation flow sheets to complete the required data set.

#### 9.1.2 Data Capture Methods

Data will be prospectively entered into a secure web-based database (REDCap <https://redcap.health.uq.edu.au/>), hosted by the University of Queensland. Printed paper CRFs will be available if required.

### 9.2 Data Storage

Hard copy data will be securely stored by the investigating site in a locked cupboard in a secured location. Electronic data will be securely stored on the RedCAP database, hosted by the University of Queensland.

### 9.3 Sample Storage

Biological sample processing and storage will follow standard operating procedures. The samples are kept in a security protected freezer in the each institution, and will be transferred in batch every 12 months to a dedicated security protected freezer at the Centre for Children's Health Research

Centre, Brisbane, Australia. The samples will be kept for 10 years after study completion and will be destroyed thereafter. All study blood tests will be labelled with a study number, and not with an identifier containing the identity of the participant, to ensure confidentiality. Any use of the participants blood other than what is approved for this study will require further review by our ethics committee and approval.

## 9.4 Record Retention

As required by the Queensland State Archivist, all study information and documentation will be securely stored for a period of 15 years after the date of the child's eighteenth birthday. As this trial will recruit participants down to birth age, all records will be securely stored for a total of 33 years before being securely destroyed.

## 10 STUDY OVERSIGHT

The trial will be overseen by a trial steering committee (TSC), the membership of which will include: the CIA, and at least 2 further CIs. The role of the TSC will be to: monitor and supervise progress of the trial; review at regular intervals relevant information from other sources.

The statistician and secretariat will be appointed once the study has authorisation to commence. Prior to the commencement of the study, the DSMB Terms of Reference (ToR) and Standard Operative Procedures (SOP) will be distributed.

The trial will be coordinated at each site by an on-site Study Management Team consisting of, at a minimum, the site PI and a site study coordinator/research assistant, and an expanded group including a representative each of perfusion, PICU, and cardiac surgery. The site PI will be responsible for local oversight of the study including: monitoring safety; ensuring that the study is conducted according to the protocol; and ensuring data integrity. The site PI will review the data for safety concerns and data trends at regular intervals, and will promptly report to the HREC and the central coordinating team any significant protocol deviation or any other significant event or problem that arises during the conduct of the study.

### 10.1 Quality Control and Quality Assurance

To standardise the collection of data by local investigator teams, training of the site PI and research assistant will be undertaken by the central coordinating team; the site PI and site research assistant will train the remaining local investigator team in particular the senior medical staff conducting consent and randomisation.

Training of the site PI and site research assistant will include all aspects of study conduct.

Set DSMB review points on the progress and safety of the trial are after the primary outcome is known at the interim analysis. While no formal stopping rule will be used, the DSMC may recommend ceasing the trial if there is a statistically significant difference ( $p < 0.001$ ) in primary outcome between the treatment groups overall or within pre-specified age subgroups, or in case of serious adverse events. Cessation of the trial may also be recommended if there is equipment failure

or recall, or if other evidence becomes available that would make continuing the trial unethical.

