## **6 INTERVENTION**

## 6.1 Treatment arms

Patients allocated to the study gas arm will receive NO, which will be blended into the fresh gas flow kept at 3L/min for the CPB oxygenator with NO levels maintained at 20 ppm via an Ikaria INOmax DSIR (Ikaria, NJ, USA) or similar device. Continuous sampling of NO and NO2 concentration will be undertaken from an access port just prior to the oxygenator. NO will be started immediately when the patient is on CPB and ceased once coming off CPB at the completion of MUFing. Patients allocated to the Placebo arm will receive standard respiratory gases (oxygen-air mix) during bypass at a flow rate of 3L/min. Partial pressures of CO2 will be maintained constantly in both study arms as per the institutional practice.

*Note:* If patients require several CPB runs during the same procedure, the treatment has to be provided for each run using the same treatment allocation for every run (i.e. patients allocated to study gas arm will receive NO at 20ppm for every run).

**Subsequent CPB procedures:** Patients that were previously enrolled and randomised into the study with surgical procedure performed that required use of cardio-pulmonary bypass will not get re-randomised. Previously enrolled and randomised patients will undergo the same treatment allocation for subsequent surgeries, unless parents opt out. The study perfusionists at each study site have access to the treatment allocation, which will remain blinded for all other study team members.

**Blinding arrangements.** Of the investigating team, only the study perfusionist will be aware of the randomisation and NO delivery. Blinding arrangements in the operating theatre will be achieved by covering the NO delivery system with drapes. The dedicated study NO delivery system will be connected to the CPB oxygenator at all times, independent of randomisation. The surgeons, anaesthetists and ICU staff will be not aware which treatment arm a patient been allocated to. The perfusionists will be advised that all aspects of CPB except for provision of NO (or not) should be performed in a standard fashion for study participants. The perfusionist does not attend the surgical handover in PICU. The Data Safety Monitoring Board will be unblinded in the event of a severe adverse event. In our pilot study and the previous published study by Checcia, methaemoglobin values using NO at 20 ppm were similar in both the control and intervention groups (1.4%) [29].

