### *Interim analyses*

Two pre-planned interim analyses were performed after the primary outcome measure was finalised for 660 and 1000 patients, respectively. Blinded interim analyses that detailed the primary outcome between treatment groups as well as information on recruitment and adverse events were presented to the Data and Safety Monitoring Board (DSMB) for their consideration. The Haybittle-Peto rule was applied (i.e. a significant p-value less than 0.001 was deemed necessary to warrant consideration of stopping the study early for benefit) (18, 19). The type I error for the final study analyses has not been adjusted to allow for interim analyses.

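### The board's set safety reviews wait for the efficacy interims at 660 and 1,000 children, so the documents schedule no comparison of harms by arm until about 52% of the trial is randomised

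*Combined protocol and SAP*

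**What the plan says.** **Timing.** Protocol section 10.1 states: "Set DSMB review points on the progress and safety of the trial are after the primary outcome is known at the interim analysis". The SAP, under Interim analyses, gives the counts: "Two pre-planned interim analyses were performed after the primary outcome measure was finalised for 660 and 1000 patients, respectively".

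**Content of the looks.** The SAP says the interim reports showed the primary outcome between treatment groups, "as well as information on recruitment and adverse events were presented to the Data and Safety Monitoring Board". A split by group is stated for the primary outcome. Whether adverse events were split in the same way is not said.

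**Thresholds.** Section 10.1 disclaims a formal stopping rule. It lets the board recommend stopping on p<0.001 for the primary outcome overall, "or within pre-specified age subgroups, or in case of serious adverse events". In the SAP, "a significant p-value less than 0.001 was deemed necessary to warrant consideration of stopping the study early for benefit". Neither document gives a numerical boundary for harm.

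**Routes for single events.**
- Section 6.1: "The Data Safety Monitoring Board will be unblinded in the event of a severe adverse event".
- Section 8.1 places death, ECLS and renal replacement among the outcomes to be expected after this surgery. It says all SAEs including deaths will be reported, without naming a recipient, and adds that "the investigators will give clinical recommendations if the death was unexpected and reason for further investigation by the DSMB".
- Section 8.4: "Any SAE occurring in a study participant will be reported to the HREC within 24-72 hours of detection". The board is not mentioned there.
- Section 8.2 gives the board oversight of performance, recruitment rate and analysis, with no meeting calendar.

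**Other oversight.** Under section 10, site principal investigators look at safety and data trends regularly, and the board's Terms of Reference and operating procedures are circulated before the study starts. The SAP lists the Terms as planned supplementary material. They are not in the file.

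**The concern.** When death, ECLS and dialysis are all foreseeable after the operation, each case in the nitric oxide arm can look unremarkable on its own. An excess shows only when the two arms are set side by side. Section 6.1 keeps allocation from everyone on the investigating team except the study perfusionist, so nobody at site level can make that comparison. The board can, but its set review points are tied to an efficacy milestone half-way through the trial.

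At stake is how long an imbalance in serious events could build up, in neonates and infants, before anyone is scheduled to look for it. The inconsistent routing adds to this. Section 6.1 turns on a *severe* event, which section 13.3 defines as a severity grade. Sections 8.1, 8.4 and 10.1 turn on *serious* events, defined in section 8.1 by outcome. One names the board and another names the ethics committee. Section 8.1 also confines adverse events to the operation and the next 48 hours, yet asks for recording until the end of participation, so a death between day 3 and day 28 is not clearly captured as an SAE.

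**Working it through.** **1. The denominator.** Section 11.2 gives 0.2 SD, 90% power, two-sided 5%, 10% withdrawals and 15% for non-normality, with a total of 1,320. Per arm, n = 2(1.960 + 1.282)² / 0.2² = 526 after rounding up.
- Adding 25%: 658 per arm, 1,316 in total.
- × 1.10 × 1.15: 666 per arm, 1,332 in total.
- × 1.15 / 0.90: 673 per arm, 1,346 in total.

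All are within 3% of 1,320, so the stated total is sound as a base.

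**2. Where the looks fall.** 660/1,320 = 50.0%; 1,000/1,320 = 75.8%.

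**3. Randomised by the first look.** Recruitment is planned over 3.5 years (section 2.1, expected enrolment) or 4 years (section 1.3). Even accrual is assumed.
- 3.5 years: 1,320/3.5 = 377 a year, or 28.9 per 28 days. 660 + 28.9 = 689 (52.2%). The 660th child is randomised at 21 months.
- 4 years: 1,320/4 = 330 a year, or 25.3 per 28 days. 660 + 25.3 = 685 (51.9%). The 660th child is randomised at 24 months.

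**4. Events before the first look.** Section 2.1 gives 2-5% perioperative mortality for children generally. Without an effect, the first 660 children yield 660 × 0.02 = 13 to 660 × 0.05 = 33 deaths. If nitric oxide doubled mortality (assumption), the excess among 330 exposed is 330 × 0.02 = 6.6 to 330 × 0.05 = 16.5, about 7 to 17.

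**5. Would the primary-outcome criterion catch this?** Death scores zero ventilator-free days. Suppose mortality is 5% against 10% and survivors are alike (assumption). The Mann-Whitney probability moves from 0.5 by (0.10 × 0.95 − 0.90 × 0.05)/2 = 0.025. Its null standard error, ignoring ties, is √[661/(12 × 330 × 330)] = 0.022, so z is about 1.1. A two-sided p<0.001 needs about 3.3.

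**6. What earlier looks could detect.** For m children per arm, mortality p₀ on control and p₁ on nitric oxide, and mean p̄, power = Φ{[(p₁ − p₀) − 1.96√(2p̄(1 − p̄)/m)] / √[(p₀(1 − p₀) + p₁(1 − p₁))/m]}. Example with 5% against 10% and m = 330: (0.05 − 1.96 × 0.0205)/0.0204 = 0.48, so power is 69%.

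| Children (both arms) | Mortality doubled | Mortality tripled |
|---|---|---|
| 100 | 8-16% | 17-38% |
| 200 | 13-27% | 30-66% |
| 330 | 19-41% | 46-86% |
| 660 | 33-69% | 75-99% |
| 1,000 | 46-85% | 90-100% |

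Ranges run from 2% to 5% control mortality. Judged at p<0.001, a doubling has only 4-20% power at 660.

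**7. A first report at six months.** Even accrual gives 330/2 = 165 to 377/2 = 189 children. Under a doubling, the excess by then is 165/2 × 0.02 = 1.7 to 189/2 × 0.05 = 4.7 deaths.

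**The case against.** **The Terms of Reference may already set earlier meetings.** Section 10.1 names set review points and does not say that the board meets at no other time. This stands as a limit on the finding. If earlier reviews exist, section 10.1 should refer to them.

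**The board is not cut off between looks.** A reader of section 8.1 might infer that only deaths an investigator calls unexpected ever reach the board. The documents do not support that. Section 6.1 unblinds the board for a severe adverse event, whether or not it is a death or unexpected. Section 10.1 lets it recommend stopping for serious adverse events, and section 8.1 promises that all SAEs are reported. What remains is that these routes respond to single events, compare no rates, and are described inconsistently. Regular review by site investigators is real oversight, but it is blinded and covers one site.

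**Early tables would seldom reveal a moderate harm.** This is correct: power for a doubling is 8-16% at 100 children. The fall in excess deaths from 7-17 to about 2-5 in steps 4 and 7 compares when someone first looks. It does not show that the harm would be recognised then.

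**Showing deaths by arm exposes part of the primary outcome.** This is also correct, since death scores zero. Boards ordinarily see deaths by arm without a test for benefit, so it is a reason for a safeguard and does not defeat the proposal.

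**Timing.** The SAP reports both interims as done, so a report running from the first randomisation can no longer be introduced. The change can serve only what remains of recruitment, and disclosure.

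**Conclusion.** The point holds in a limited form: a cheap improvement to safety oversight, and not an error in the efficacy design. Section 10.1 states a rule that ties set safety reviews to the efficacy interims. Nothing in the documents supplied schedules an earlier comparison by arm, and even the look at 660 is not clearly one for adverse events.

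The size is about 52% of children randomised at the first set review and, under a doubling of 2-5% mortality, about 7 to 17 excess deaths. This rests on even accrual over 3.5 to 4 years, on a mortality range quoted for paediatric cardiac surgery generally, and on an effect chosen only for illustration.

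Two stronger readings are not supported. The figures do not suggest that nitric oxide raises mortality: the synopsis reports a pilot trend to improved mortality, and section 6.1 reports similar methaemoglobin in both arms. Nor would the first look plausibly come as late as 3.3 years. The enrolment figures in section 2.1 (400 eligible a year × 50% = 200) give 660/200 = 3.3 years, but 200 a year would also mean 1,320/200 = 6.6 years in total, against a plan of 3.5 to 4.

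**What to change.** 1. **Section 10.1.** Add a closed, safety-only report by arm to the board at a regular interval such as six months. It should cover all-cause death to day 28, ECLS, SAEs and MetHb >3%, and carry no test for benefit. The primary outcome stays compared only at the two interims. If the Terms of Reference already provide this, cite them.
2. **Sections 6.1, 8.1, 8.2 and 8.4.** Reconcile them so that one defined term is used and every death and SAE is copied to the board as well as reported to the ethics committee.
3. **SAP, Interim analyses.** State whether adverse events were shown by arm at 660 and 1,000.
4. **If recruitment has passed these points.** Apply the report to what remains, and disclose the board reviews actually held and what they contained.

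**Cost.** A short table from data already entered in REDCap, and some board time. The downsides are low power early on, so protection is mainly against large harm; more occasions to see a chance imbalance in rare events; and partial sight of the primary outcome through deaths, which is why no test for benefit should be attached.
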